#### Exit interviews

A trained data collector conducted exit interviews. At each PHC, the data collector recruited NCD patients over a period of three days per PHC for all the PHCs (*n* = 39). Each patient exiting the facility was approached. If the current consultation was for Diabetes/Hypertension, then the study details was explained and written consent obtained to conduct the interview. The target was to interview 30 patients but we were able to conduct, on an average, eight interviews per PHC over the three days. A daily debrief was organised by the researchers to identify and respond to any ethical or operational challenges in course of the day.

##### End-line survey

After 18 months of the intervention, the survey will be conducted in the same three talukas. The same households (panel survey) that participated in the baseline survey will be visited again with the survey questionnaire.

#### Qualitative data

Qualitative data will be collected in two phases; it will be used on one hand to guide the contextualisation of the intervention, and on the other hand for a process evaluation of the intervention.

Initially, we used data from focus group discussions and in-depth interviews with communities and health managers to contextualise the implementation of the intervention. The data was also used to prepare an initial programme theory (how is the intervention supposed to work). After the implementation of the intervention, we will use qualitative data to understand why it worked in some places (where it did) and not in others (where it did not) through the refining of the initial programme theory. The refining of the initial programme theory involves critically assessing the assumptions of the initial programme theory in relation data collected during the intervention implementation as well as an understanding of how such interventions are supposed to work in wider literature. Programme theories can be progressively refined as the intervention is implemented and monitored. The refined theories generated could be used to understand the relationships between intervention inputs, local context and the outcomes seen [29, 35, 40].

For developing the initial programme theory, we will conduct a content analysis of relevant documents including project documents, documents and reports of the National Programme for Control of Diabetes Cardiovascular diseases and Stroke, the recently launched national programme on NCDs and various pharmaceutical policies at state and national level. The content analysis will be used along with review of literature and the baseline qualitative data to build an initial programme theory on why the intervention is *supposed* to work and what possible local factors could be critical for the implementation of NCD care at PHCs.

In-depth interviews, process documentation during the implementation of the intervention and another round of qualitative data collection through focus group discussions and in-depth interviews at the end of the intervention period will be used to refine the initial programme theory and understand the health system factors that could have contributed to positive outcomes in PHCs where it did work, and the possible contribution of the intervention.

##### Focus group discussions

As part of the baseline activities, we conducted focus group discussions (FGD) with various stakeholders such as community members, health workers, government doctors (PHC medical officers) and pharmacists in private pharmacies. A total of 13 FGDs were conducted. Each FGD had about 8–10 participants.

The FGDs among the community members were conducted with an objective of understanding the experience and identifying barriers in accessing care at PHCs, more so for patients with NCDs. We in fact tried getting different perspectives by conducting these FGDs among diverse groups i.e. men, women, NCD patients, healthy adults, and people from different socio-economic categories. The health workers FGD consisted of Accredited Social Health Activist (ASHAs) and Auxiliary Nurse Midwife (ANMs). The discussions with the PHC medical officers were conducted separately. These FGDs focused on PHC doctors’ experiences and challenges in delivering care for patients suffering from NCDs at primary care level, including pharmaceutical and behavioural management. Their perspectives on access to medicines in general and on services delivered at the PHC were also documented. We invited pharmacists who owned or operated private pharmacies in Tumkur town to participate in an FGD. In this FGD, we explored their perceptions on price and quality of the medicines supplied both in government and private pharmacies and also on their view on generic medicines.

All FGDs were audio-taped and transcribed. The participation in the FGDs was voluntary and no compensation was provided to the participants. Informed written consent was obtained from all FGD participants. All participants were given written information about the project. The details of the FGDs conducted in the baseline phase are in Table 8.

**Table 8 Tab8:** Details of focus group discussions conducted in the baseline phase

S No.	Number	Group	Content	Target population
1	2	Patients	NCD burden & care	NCD patients
2	2	Healthy adults (Non NCD)	Quality of health care	Non NCD patients & other healthy individuals
3	4	Health workers	NCD burden & community awareness	ASHAs and ANMs
4	1	Private drug shopkeepers	Quality generics for NCD	Tumkur district private drug shopkeepers

##### In-depth interviews

In-depth interviews were conducted with various actors in the heath system to understand their perspectives on different issues around NCD management and access to medicines. Suggestions were sought from them on the design and implementation of the study intervention to improve access to medicines for NCD patients. The feasibility of the intervention was discussed and the suggested modifications were incorporated.

#### Process documentation

Process documentation forms an integral part of the qualitative component of this study. Quarterly field visits will be conducted to the PHCs and data on utilisation of various services and medicines dispensed for NCDs will be recorded. The patient experiences, PHC staff attitudes towards NCD patients and details of supervisory visits from taluka health officials would be captured. The latter is in order to understand and interpret possibly taluka-wise differences in local leadership and management that could explain differences in performance between PHCs that have received similar inputs.

The interaction with the providers would focus on the motivating factors in case of early adopters and the perceived difficulty in case of others. After each such visit, a detailed narrative report would be prepared. This report would capture unstructured details about: new changes or updates regarding NCD patients in the PHC, responses of PHC staff to the intervention-related developments such as PHC meetings, sub-centre meetings and PHC health days (in the intervention PHCs). In the control PHCs, the field visits will be used to collect new information on any initiatives to detect or treat NCD patients and perspectives on the staff on NCD care.

As part of the community level intervention, we will participate in the patient group meetings and observe whether the group dynamics and the interaction of the group with the PHC have changed/improved, this will be noted and these groups will be purposively approached during the post-intervention data collection.

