### Study design and conceptual framework

In this study, we use a quasi-experimental approach along with a theory-driven evaluation to study an intervention for improving access to medicines for diabetes and hypertension at PHCs in Tumkur district of Karnataka, India. We will use a quantitative before-after quasi-experimental study design to understand determinants of improved access to medicines, and a qualitative theory-driven evaluation approach to answer the *how* questions. All PHCs (39 PHCs) across three selected *talukas* were randomly assigned to one of three arms of the intervention. A baseline and an endline survey of households, PHCs and private pharmacies will be conducted for the before-after quasi-experimental component.

The qualitative component of the study will use a theory-driven approach to understand and explain the changes if any, and why the intervention worked for some (where it did) and not for others (where it did not) across the three arms of the study. The theory-driven approach uses successive waves of qualitative data to refine the programme theory, thus resulting in a contextual explanation for how the programme worked in the given setting [25]. In so doing, we shall generate an explanatory theory about improving access to medicines in local health systems in India especially focusing on what works, for whom, and under what conditions, and why. The study design and initial programme theory have been represented in Fig. 2 and Fig. 3. An initial programme theory is an explanation of why the programme is expected to work; it takes into consideration the inputs of the intervention and the assumptions of the implementers on how the intervention inputs could result in the expected outcomes, integrating contextual information from the implementation setting.

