### Data collection and tools

The study tools, study preparation, process of data collection are described below (See also Fig. 7 on the study timeline). The quantitative data collection includes household surveys, facility surveys (public and private pharmacies) and exit interviews at PHCs. The qualitative component includes focus group discussions (FGD) with district-level officials, PHC staff and patient groups.

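### The rule for approaching patient groups at endline reads as selection on observed improvement, with no provision for groups that stayed the same or worsened

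*Protocol article*

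**What the plan says.** The last paragraph of Process documentation concerns the community-level intervention. The team will take part in patient group meetings and "observe whether the group dynamics and the interaction of the group with the PHC have changed/improved". The sentence then continues that what is seen will be noted, and it states who is approached later: groups that "have changed/improved, this will be noted and these groups will be purposively approached during the post-intervention data collection".

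The aim these data serve is given under Study design and conceptual framework. The qualitative component is to explain "why the intervention worked for some (where it did) and not for others (where it did not) across the three arms of the study". The Qualitative data section repeats this two-sided aim for the period after implementation. A later sentence of that section, on refining the programme theory, names only one side: the health system factors that "could have contributed to positive outcomes in PHCs where it did work".

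Table 3 lists the formation of NCD patient groups as an input of Arm B only.

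**The concern.** An explanation of why something worked in some places and not in others needs cases of both kinds. If endline patient groups are approached because they were seen to improve, there are no contrast groups within that source. A feature shared by the improved groups may then look like a condition for success when it is simply common in the area. Members of a group that stalled are best placed to say why it stalled, and the rule makes no provision for hearing them at endline.

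Patient groups are central to the study's questions. The first objective asks whether and how forming such groups could improve drug availability at PHCs. The second sub-question asks how patient pressure groups can be formed and whether that improves availability. Group formation is also part of what separates Arm B from Arm A. At stake is the study's ability to say how, for whom and under what conditions the patient-group component works.

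**Working it through.** No arithmetic applies. The article gives no number of patient groups, no number of endline discussions and no expected share of improved groups. The check is a reading of the relevant sections against each other.

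1. **The criterion.** The word *purposively* means selection by some criterion. The only criterion in the sentence is observed change or improvement. If every observed group were to be approached, the word would have nothing to do. Selection on improvement is therefore the natural reading.

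2. **The ambiguity.** The team observes *whether* change occurred, so what is noted may be either answer. *These groups* can refer back to all groups whose meetings are attended, and *changed* does not have to mean improved. The wider reading is possible. Neither reading comes with a statement that unchanged or worsened groups will be approached.

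3. **Who judges.** The judgement comes from team members who take part in the meetings. The sentence names no measured PHC outcome as a basis for selection, and the Data analysis section says the quantitative and qualitative analyses are first done independently.

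4. **Fit with the aim.** The aim is two-sided, covering places where the intervention worked and places where it did not. The selective reading supplies one side for this source. The sentence about positive outcomes in the Qualitative data section leans the same way.

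5. **What else is collected.**
   - Quarterly PHC visits record service use and patient experiences and are not limited to improved PHCs. Control PHCs are visited too (Process documentation).
   - Provider interactions cover "motivating factors in case of early adopters and the perceived difficulty in case of others".
   - The endline includes "another round of qualitative data collection through focus group discussions and in-depth interviews at the end of the intervention period", with no stated restriction to improved sites.
   - The qualitative analysis plans to look for contradictions to the programme theory as well as support for it.
   - The household panel is surveyed again at endline, and the quantitative and qualitative results are then integrated.

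6. **What these sources do not replace.** Provider accounts and field notes on a stalled group are not its members' own account, and a search for contradictions can use only the data collected. The compensation is real but partial.

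7. **Reach.** The difference-in-difference and intention-to-treat analyses do not use this sampling rule and are unaffected.

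**The case against.** The strongest case on the other side has three parts.

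First, the sentence never says that groups are chosen because they improved, and it excludes no one. With *whether* in view, it may simply mean that the attended groups will be revisited. This stands as a reason for caution: selection on improvement is an inference from an ambiguous sentence, though the more natural one.

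Second, a reader might infer that the whole explanation rests on successful sites, that features of unchanged groups go unseen, or that there are no patient data from places where the intervention failed. The documents do not support any of these. Unchanged groups are observed in their meetings during the intervention, and the quarterly visits, non-adopter accounts, control-PHC visits, wider endline discussions and household panel are not confined to successes. A reader might also infer from Data collection and tools, which lists patient groups among the focus group participants, that endline patient accounts come only from Arm B. That does not follow: the section describes the qualitative component as a whole, Table 8 shows baseline discussions with NCD patients in general, and the abstract speaks simply of patients.

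Third, a journal article condenses the full protocol, and a detailed qualitative sampling frame is commonly left there. That is right for numbers of discussions and similar detail. It does not dispose of the point, because the article itself states a rule, and the rule as worded sits badly with the aim.

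**Conclusion.** The point holds in a limited form. As worded, the rule most naturally selects Arm B patient groups for endline data collection on the result to be explained, by the attending team's impression, and provides for no contrast groups. That weakens one qualitative source, in one of three arms, for an objective in which patient groups are the subject. Other sources compensate in part.

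The conclusion rests on the natural reading of one sentence. If all observed groups were meant, the defect is only one of wording, and the same edit settles it. The size cannot be quantified from the document. The change is worth making because it costs almost nothing and serves the study's own question of how, for whom and under what conditions the intervention works.

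**What to change.** Reword the last sentence of Process documentation along these lines: *After the intervention, patient groups will be purposively chosen to include both groups judged changed or improved and groups judged unchanged, worsened or non-functional. The same topic guide will be used for all, within the planned number of discussions.* If the intention was to approach every observed group, say so instead.

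This changes the wording of the qualitative sampling rule only. It adds no discussions and leaves the surveys and quantitative analyses as they are. The small downside is that, with the total held fixed, fewer discussions will be with improved groups.

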#### Drug quality test

A quality test for NCD medicines has been planned as an independent activity of the study. Of the 11 drugs included in the facility survey, four were chosen (two anti-diabetic and two anti-hypertensive medicines) for quality testing. Generic and branded medicines were sampled from both government and private facilities in the three study talukas, Tumkur district as well as the nearest big city, Bangalore. The full details of the sampling and the tests are in Additional file 9.

### Data analysis

The quantitative and qualitative analysis will first be done independent of each other. At the end of the baseline survey and during process documentation, the qualitative data will be analysed iteratively for refining the programme theory of the intervention.

#### Data entry and cleaning

The original household survey data were labelled and stored so that researchers can return to the original source of the data if necessary. A data entry form with inbuilt restrictions and validity checks for the fields was created using Epidata [41]. In addition, 10 % of the data entered randomly were verified with the survey questionnaire by a supervisor. Any discrepancy (missing or illogical values) was corrected by checking the paper questionnaire and if any crucial missing data, field visits may be made again, if necessary.

#### Quantitative data analysis

The quantitative data will be transferred to data analysis software (SPSS) and basic variables will be created. All the codes and value labels of the variables will be recorded and saved for further use if any. We will create three datasets from the household survey to capture basic household, demographic and patient (NCD) level characteristics. Then, these datasets will be merged and the merged dataset will be independently validated through running similar queries on at least two different statistical analysis software (SPSS and R). Private facility interview data and PHC interview data will be merged after cleaning. Exit interview data will be also be cleaned and analysed separately.

#### Univariate analysis

Basic tables and graphs depicting summary statistics of the respondents (individuals, households and patients) will be done– example percentage of women, age distribution, caste, religion, type of households, household amenities, number of diabetics and hypertensive, availability of medicines in the house and health facilities etc.

#### Bivariate analysis

We will check for association (Chi-square distribution) and linear and partial correlations among selected variables in line with the hypotheses/research questions identified in the research protocol. Baseline and end-line household and facility level characteristics will be compared across the intervention arms and study talukas.

#### Intention-to-treat analysis

We will conduct an intention to treat analysis at the PHC level. Independent variables such as socio-demographic characteristics will be compared to assess comparability across intervention arms, using relative risk ratios at baseline and endline. Like in the cases of classical trial studies, when the unit of the intervention (PHCs in this study) does not follow the protocol for their assigned treatment/ intervention, the resultant “treatment contamination” can produce misleading findings. Intention to treat analysis will be used in this case to estimate the effect of recommending a treatment to study participants, not the effect of receiving the treatment. Further a technique called *contamination adjusted intention to treat analysis* will be attempted to complement the intention to treat approach by producing a better estimate of the benefits and harms of receiving a treatment/intervention [42].

#### Subgroup analysis

We will analyse various sub-groups like gender, age, caste, socio-economic category, distance of household from PHC, in relation to their access to medicines, affordability, or availability of key medicines for previous six months. We will compare these sub-group characteristics across intervention arms.

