#### Research questions

The main research question of the study is: *does a package of interventions involving health services optimisation and strengthening community participation platforms at primary care level improve availability*, *affordability*, *utilisation and compliance of good quality generic drugs for NCDs in government facilities in Karnataka*? *If yes*; *how*, *and for whom and under what conditions does this happen*? We further developed five specific sub-questions in line with the main research question (and our study objectives listed above) as follows:Does optimisation of health services (announcing monthly NCD clinic days, increasing consultation time, providing counselling services and ensuring continuity of care) improve utilisation of drugs and their compliance among patients with NCDs?How can existing community participation arrangements be strengthened to form pressure groups of patients with chronic diseases at PHCs? Does this improve availability of drugs at these PHCs?If NCD patients shift or opt for public sector generic drugs for NCD care, will their OOP expenditure on NCD medicines and proportion of total household expenditure (THE) spent on NCD drugs decrease?Does the routine monitoring of the quality of NCD drugs strengthen the regulation of other drugs? How does the quality of drugs provided in government hospitals compare with those commonly bought over-the-counter in private pharmacies?How do private pharmacies respond to improved generic drugs availability and utilisation in government PHCs? Do the mean prices of essential NCD drugs and their availability change in response to improved availability of these in PHCs?What is the marginal cost of strengthening health systems so that access to medicines can be improved?

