#### Outcome estimation

Outcomes (see Table 9) will be reported as effects of said interventions and represented as risk ratios and odds ratios with 95 % confidence interval.

**Table 9 Tab9:** Measures (indicators) for primary and secondary outcome of interest

Factors to be measured	Indicator
Primary outcome of interest	
Improved and continuous availability of generic drugs at PHC	Percentage of PHC where all generic medicines for NCD patients adequately available in last three months
Increased and regular access to quality medicines for patients with NCD	Percentage of NCD patients/patient groups visit intervention PHC in last three months
Out-of-pocket expenses among patients with NCD	Percentage reduction in median OOP expenditure on medicines per year among NCD patients.
The marginal cost of the intervention to that of the outcome	Incremental cost effective ratio
Improved compliance to standard treatment guidelines by the PHC	Percentage MOs followed prescription practices as per the standard treatment guidelines.
Improved demand of generic drugs among the patients	Percentage increase in patients availing generic drugs from the PHC compared to what it was at three months back
Improved utilization of medicines among NCD patients	Percentage of NCD patients/ patient groups obtained complete and regular medication for last three months.
Secondary outcome of interest	
Better coordination among health staffs with regards to NCD patient group formation	- Percentage increase in number of patient groups formed. - Percentage increase in number of new diabetes patients registered in last three months for a given PHC. - Percentage increase in number of new hypertension patients registered in last three months for a given PHC.
Better drug procurement	Percentage PHCs where drug procurement is up to date for the last quarter.
Conduction of NCD clinics	Percentage PHCs conduct NCD days in last three months
Better reporting and recording by the pharmacists at PHC	Percentage PHCs where medicines were dispensed as prescribed

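### The planned subgroup analysis does not contrast the intervention effect between subgroups, so it gives only descriptive support for the who-benefits part of the main question; its six-month window also differs from Table 9

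*Protocol article*

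**What the plan says.** The main question (Research questions) asks whether the package improves availability, affordability, utilisation and compliance. If the answer is yes, it goes on to ask how, "and for whom and under what conditions does this happen". Study design and conceptual framework gives the same theme to the theory-driven qualitative work, "especially focusing on what works, for whom, and under what conditions, and why".

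Subgroup analysis consists of two statements. The first names five factors: "We will analyse various sub-groups like gender, age, caste, socio-economic category, distance of household from PHC". These are examined "in relation to their access to medicines, affordability, or availability of key medicines for previous six months". The second gives the comparison by arm: "We will compare these sub-group characteristics across intervention arms".

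Other sections bear on how this is read:
- Intention-to-treat analysis already compares socio-demographic characteristics across arms at baseline and endline, to judge comparability. Bivariate analysis compares household characteristics across arms as well.
- Difference in difference analysis names the estimator of the intervention effect and does not mention subgroups.
- Table 9 (Outcome estimation) defines the primary availability indicator as "Percentage of PHC where all generic medicines for NCD patients adequately available in last three months". PHC visits and complete, regular medication also use three months. Out-of-pocket expenditure is per year.

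**The concern.** Asking for whom the package works is asking about effect modification: is the change attributable to the intervention larger in one kind of patient than in another? That calls for a contrast of effects between subgroups. The section states a different comparison and does not link it to the difference-in-difference estimator.

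If the results are separate arm comparisons within each subgroup, a significant result in women and a non-significant one in men is easily reported as a benefit for women only. Such a pattern is common when the true effect is the same in both. In a study that aims at equitable access, a spurious statement of this kind about caste, socio-economic category or distance could mislead planners. It could also send the qualitative work looking for an explanation of a difference that does not exist.

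A second, unrelated problem sits in the same section. The six-month window does not match the three-month windows in Table 9, so a subgroup result could not be set directly beside the corresponding overall result.

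**Working it through.** **Two readings of the stated comparison**

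1. *Literal.* Gender, age, caste, socio-economic category and distance are tabulated by arm. This is a balance check, largely planned already under Intention-to-treat analysis and Bivariate analysis. It involves no outcome and so says nothing about who benefits.
2. *Generous.* Taken with the statement before it, subgroup-specific outcomes are compared by arm. This gives one arm comparison per subgroup, which is informative descriptively. It does not estimate the difference between those comparisons or its uncertainty.

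Neither reading produces an arm-by-subgroup contrast.

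**How often within-subgroup results disagree when the effect is the same (illustration)**

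The documents give no power, effect size or intracluster correlation; Household survey sets the sample by a household count only. Assumptions: two-sided 5% test, two equal and independent halves, identical true effect.

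- Expected overall z = 1.96 + z(power).
- Power in each half: p = Φ(z/√2 − 1.96).
- Chance that exactly one half is significant: 2p(1 − p).

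| Assumed overall power | z | p in each half | 2p(1 − p) |
|---|---|---|---|
| 50% | 1.96 | Φ(−0.574) = 0.283 | 0.41 |
| 80% | 2.80 | Φ(0.021) = 0.508 | 0.50 |
| 98% | 4.01 | Φ(0.878) = 0.810 | 0.31 |

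Over this range, a given factor shows a spurious split between roughly three times in ten and one time in two.

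**How precise the proper contrast would be (illustration)**

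The household counts reproduce: 39 × 30 = 1170 (target), and 326 + 482 + 261 = 1069 (surveyed, Table 4). Per arm, 1069/3 ≈ 356. Assumptions not in the documents: control proportion 30%, two equal subgroups, design effect 1 to 3, and a simple endline comparison.

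- Overall difference of 15 points (30% against 45%): power = Φ[(0.15√m − 1.96√(2 × 0.375 × 0.625))/√(0.21 + 0.2475)]. With m = 356 this is 99%; with m = 356/3 ≈ 119 it is 67%.
- Difference between subgroups, with 15 points in one half and none in the other: SE = √[(2 × 0.21 + 0.21 + 0.2475)/(m/2)]. This is 0.070 at m = 356 and 0.122 at m = 119. Power = Φ(0.15/SE − 1.96) = 57% and 23%.

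The contrast is therefore a different and harder analysis than an arm comparison, which is why it should be labelled exploratory.

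**Windows side by side**

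Subgroup analysis has "availability of key medicines for previous six months"; Table 9 has "adequately available in last three months". The mismatch is on the page. The Table 9 availability indicator is a property of the PHC: all patients of one PHC share its value, so it cannot differ between men and women, or between castes, within that PHC.

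**The case against.** The strongest reply is that this is loose wording in a condensed article. The first statement of the section ties subgroups to outcomes, and because a balance check is already described elsewhere, the literal reading is the less likely one. Interaction terms and clustering are commonly left to an analysis plan, and nothing here excludes them or says that significance in one subgroup alone will be read as a differential effect.

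Much of that stands. The absence of a model formula is not the point. What remains is that the section does state a comparison, and on either reading it is not the one that the main question needs.

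A reader might infer more, in three ways that the documents do not support:

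- *That the study cannot answer who benefits.* Subgroup outcomes by arm would inform the question descriptively, and the qualitative evaluation is assigned it too.
- *That five factors make a false split almost certain*, by 1 − 0.5⁵ = 0.97. This treats the factors as independent, but all five split the same households and share one overall estimate. Simulating five unrelated equal splits around a shared overall effect gives about 83% at 80% power, 73% at 50% and roughly 60% at 98%. These figures still rest on assumed power and binary factors, so no cumulative figure should be carried forward.
- *That the six-month window is why effect modification cannot be assessed.* A recall window has no bearing on that. The two sections may also measure different things, patient-level access in one and PHC stock in the other.

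**Conclusion.** The point holds in a limited form. As worded, Subgroup analysis does not contrast the intervention effect by gender, age, caste, socio-economic category or distance. Its quantitative contribution to the who-benefits part of the main question is therefore descriptive. It is the only quantitative section on patient subgroups, so the wording deserves correction, although the question does not rest on it alone.

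The size of the risk is illustrative: about 50% per factor for a spurious split at an assumed 80% overall power, 41% at 50% and 31% at 98%, given two equal independent halves. That the study would publish such a split as a finding is not something the text commits it to.

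The six-month against three-month mismatch is confirmed. It is a separate, smaller inconsistency.

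**What to change.** Reword Subgroup analysis as follows.

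1. For the patient- or household-level outcomes in Table 9 (PHC visits, complete and regular medication, out-of-pocket expenditure), estimate the arm-by-subgroup contrast for each named factor within the difference-in-difference model, that is, the arm × time × subgroup term.
2. Cluster standard errors at PHC level, the unit that was assigned to arms.
3. Report each contrast with its 95% confidence interval and label it exploratory. Within-subgroup estimates may be shown beside it as description.
4. Separately, reconcile the six-month window with the three-month windows in Table 9, or state why it differs. Do not apply the PHC-level availability indicator to patient-level subgroups such as gender, age or caste.

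The cost is a change of wording and one added term in models already planned; the contrast needs no new data. The downside is imprecision: with 39 PHCs in three arms the intervals will be wide, and an interval that includes no difference should not be read as evidence of a uniform effect.
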